Each DSP covered a variable number of specific communities, so the third stage of sampling was to select a single community within each of the 34 DSP where the project will be conducted. The criteria for selecting the 34 specific communities (‘primary sampling units’) included 1) having a mean age of community members similar to that of the entire DSP; 2) having a population of at least 3250 adults who are permanent residents (the minimum estimated sample required to enrolled 2500 adults); and 3) having local health institutions with sufficient human resources to perform the enrollment and follow-up procedures that are willing to participate in the project.

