All permanent residents of the target communities meeting the inclusion and exclusion criteria will be eligible for inclusion in the cohort. Permanent residents meeting these criteria will be identified from the registers of residents in community health centers (which list virtually all permanent community members). Initially 3250 eligible individuals will be randomly selected from the lists of residents: after listing all adult eligible residents the total number of listed residents is divided by 3250 and the resultant integer and its fractional component (x.yy) are used to assess the proportion of the total list from which each x^th^ individual should be selected and the proportion of the total list from which each (x + 1)^th^ individual should be selected to arrive at a total sample of 3250. As many of these individuals as possible will be recruited into the project, even if the number of enrollees exceeds the minimum required sample of 2500 individuals. If contacting the 3250 eligible individuals does not result in enrolling 2500 individuals, an addition number of individuals from the resident list who were not selected the first time will be randomly selected in the same manner and invited to participate (considering the potential non-response rate of 30%, the additional number will be defined as 1.3 times of the differences between 2500 and actual number); this process will be repeated as needed until 2500 individuals have been enrolled. Reasons for non-enrollment and for post-enrollment drop-out will be described and the potential effects of selective enrollment and dropouts on the representativeness of the sample will be assessed by comparing the demographic characteristics of enrolled individuals with those of individuals who are selected for recruitment but not enrolled and of persons who drop out after enrollment with those of individuals who continue in the cohort.

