#### Enrollment and baseline evaluation

Residents of the 34 primary sampling sites who meet the inclusion and exclusion criteria will be randomly selected from lists of community members registered in the public health system (described above) and invited to participate in the project. To improve the response rate, prior to the enrolment advertising billboards will be set up at the local health service center and messages introducing the study will be sent to all community members via WeChat (social media) site. Enrollment and baseline data collection included the following steps (see Fig. 2):A)Basic information (e.g., name, age, address, phone number) of residents in the community is extracted from the community health service center (which typically have a registry of virtually all permanent residents in each community).B)Among the permanent residents 18 years of age or older, 3250 individuals will be randomly selected from the registry of residents maintained by the local health authorities.C)Researchers make phone calls to selected residents to introduce the China Depression Cohort Study-I and – if the individual expresses interest in participating – to invite them to the local community health service center for an intake interview. Researchers and community health care workers will make home visits to invite individuals who cannot be contacted by phone.D)When potential participants visit the community clinic they will be provided with details about the project and asked to sign a written informed consent.E)Baseline assessments of consenting participants are typically conducted at the local health clinic on the same day as enrollment. They include the following:Community clinic physicians conduct a physical exam, measuring weight, height, heart rate and blood pressure.Research nurses collect biological samples of blood, urine and faeces.Trained researchers instruct participants in the use of the online Participant Module and supervise their completion of self-report questionnaires about their demographic characteristics, environmental exposures, and mental health symptoms.Community clinic doctors conduct a psychological evaluation using the expanded version of the 12-item General Health Questionnaire (GHQ-12) [34, 35], which consists of the original Chinese version of the GHQ-12, and 12 additional items to improve its sensitivity. The 12 supplemental items include 6 items described in previous studies [34, 36] (respondents' subjective report of their physical health in the past month; respondents' subjective report of their psychological health in the past month; obsessive thoughts or compulsive behaviors in the last month; restriction of activities because of phobias in the past month; feelings of extreme nervousness or anxiety in the last six months; and social problems due to drinking in the last year), and 6 items developed for the current project based on expert consultation (feeling depressed or down for at least two weeks; seeking help from others due to psychological problems; hospitalization due to psychological problems; suicidal behaviors such as self-poisoning or self-injury; intention of self-harm or suicide; family history of mental disorders such as depression). The 12 GHQ-12 items are each scored as 0 (not present or mild) or 1 (present to a moderate or significant degree); so the total GHQ-12 score ranges from 0 to 12. Each participant will be classified as low-risk of depression (a GHQ-12 score of 0 to 1 and none of the 12 additional items present), moderate-risk of depression (a GHQ-12 score of 2 to 4 and none of the 12 additional items present), or high-risk of depression (a GHQ-12 score of at least 5 or a positive score on any of the 12 additional items) [36].Formal diagnostic examination by a psychiatrist using the SCID-5-CV interview schedule will be conducted in all participants classified as high-risk of depression, in 40% participants classified as moderate-risk of depression and in 10% participants classified as low-risk of depression. Similar to other two-stage epidemiological studies [34, 36], higher proportions of individuals at higher risk of depression are administered the definitive diagnostic interview; this method allows for an efficient use of the limited number of psychiatric personnel available while allowing for accurate prevalence estimates for the total population (by estimating the rates of false positive GHQ-12 rates in the high-risk group and rates of false negative GHQ-12 rates in the moderate- and low-risk groups).All high-risk participants are referred for a brain MRI scan at a regional hospital, and low-risk and moderate-risk participants are given the option of a referral for a brain MRI scan.

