#### Data analyses

Three main analyses will be conducted. P values of < 0.05 will be considered statistically significant.

The first set of analyses will describe the characteristics of participants and the detailed epidemiology of depression, including the prevalence, incidence, regional characteristics, and trends in the demographic characteristics of depression over time. Means and standard deviations will be used to describe continuous variables, and numbers and percentages will be used to describe categorical variables. Poststratification weights will be used to estimate the national prevalence and incidence of depression. Latent variable analyses and disease trajectory analyses will be used to describe the changes of depressive disorders over time.

The second set of analyses will 1) identify risk factors that influence the onset, severity and course of depressive disorders; 2) identify characteristics that can help distinguish distinct subtypes of depression; and 3) assess potential pathophysiological mechanisms that link the different types of factors associated with depression – external environmental factors, social factors, psychological factors, and biological factors. T-tests, analyses of variance, Kruskal–Wallis tests and Chi-square tests will be used to analyze differences between groups. Correlation analyses will be used to check correlations between variables. To identify potential risk factors for depression, Cox regression analyses will be used to estimate the hazard ratios (HRs) of the association of specific bio-psycho-social risk factors with the diagnosis of depression. Logistic and liner regression will be used to identify factors associated with the severity or depressive episodes. Genomic analysis (including GWAS analysis, Mendelian Randomization), metabolomic analysis and gut microbiome analysis may also be used to explore potential biological mechanisms of depression.

The third set of analyses will use the findings about risk factors to generate and test different prediction tools of depression. Different predictive models will be generated using machine learning algorithms, including Support Vector Machine, Decision Tree and Random Forest algorithms [37, 38]. Performance of the different models will be compared using the area under the receiver operating curve, prospective prediction results (sensitivity, specificity, accuracy, positive predictive value, negative predictive value) and decision curve analysis (DCA) [38].

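### The register draw uses two sampling intervals within one list, so residents of the same community have unequal selection probabilities (up to 2:1 in the initial draw)

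*Protocol article*

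**What the plan says.** The Sampling method section calls the draw random: "Initially 3250 eligible individuals will be randomly selected from the lists of residents". It then gives the mechanism. The list size is "divided by 3250 and the resultant integer and its fractional component (x.yy) are used to assess the proportion of the total list" to be taken at each of two intervals. The first share is "the proportion of the total list from which each x^th^ individual should be selected" and the second is "the proportion of the total list from which each (x + 1)^th^ individual should be selected to arrive at a total sample of 3250".

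If fewer than 2500 people enrol, further residents are drawn by the same method from those not yet selected. Each top-up is 1.3 times the shortfall, and the process repeats until 2500 have enrolled. A community qualifies by "having a population of at least 3250 adults who are permanent residents", so lists only a little longer than the initial draw are allowed.

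The Enrollment and baseline evaluation section adds only that "3250 individuals will be randomly selected from the registry of residents". The Data analyses section says: "Poststratification weights will be used to estimate the national prevalence and incidence of depression". It names no other weight and does not list the poststratification variables.

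**The concern.** Two intervals on one list give two sampling rates. Where the whole part x is 1, one part of the register is taken in full and the other at one in two. If the two parts differ in depression prevalence, the unweighted community estimate is pulled towards the more heavily sampled part, and a larger sample does not cure that.

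The step matters because the Discussion concedes that surveillance points and communities were not selected strictly at random. The draw of residents therefore carries most of the study's claim to probability sampling. The planned representativeness check compares enrolled people with those selected but not enrolled, and drop-outs with those who stay. It cannot detect a distortion in who was selected.

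**Working it through.** **Inputs.** Draw n = 3250, minimum list 3250, enrolment target 2500, top-up factor 1.3 (Sampling method); non-response 30% and prevalence 2.1% (Sample size). The list size N is not given, so it is varied. A random start within each part is granted to the plan.

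**The rule.** Write N/3250 = x + f, with x the whole part and f the fraction. Let a be the number of residents in the part taken at every x-th. The draw must total 3250:

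a/x + (N − a)/(x+1) = 3250, so a = x[(x+1)·3250 − N].

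**Reproducing the plan's 3250.** For N = 4875, x = 1 and f = 0.5, so a = 2·3250 − 4875 = 1625. The draw is 1625/1 + 3250/2 = 3250, as planned.

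**Selection probabilities.** These are 1/x and 1/(x+1), with ratio (x+1)/x.

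| N | x | Share of list at interval x | Share of draw from it | Probabilities | Ratio | Equal probability 3250/N |
|---|---|---|---|---|---|---|
| 4000 | 1 | 2500/4000 = 62.5% | 2500/3250 = 77% | 1 and 0.5 | 2.0 | 0.8125 |
| 4875 | 1 | 1625/4875 = 33% | 1625/3250 = 50% | 1 and 0.5 | 2.0 | 0.667 |
| 8125 | 2 | 3250/8125 = 40% | 1625/3250 = 50% | 0.5 and 0.333 | 1.5 | 0.4 |
| 17875 | 5 | 8125/17875 = 45% | 1625/3250 = 50% | 0.2 and 0.167 | 1.2 | 0.182 |

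When f = 0 the whole list is taken at one interval and there is no difference.

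**Precision.** The Kish weighting effect is 1 + f(1−f)/(x+f)². Its largest values are 1.125 at x = 1 (f = 1/3), 1.042 at x = 2 and 1.002 at x = 10. The loss is small.

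**Top-ups, N = 4875, 30% non-response.** The initial draw enrols 0.7·3250 = 2275. The first top-up is 1.3·225, rounded up to 293, and brings enrolment to 2480.1. The next two are 26 and 3, reaching 2500.4. The fully taken part has nobody left, so all 322 come from the other part, whose average selection rate becomes (1625+322)/3250 = 0.599. The ratio falls from 2.00 to 1/0.599 = 1.67. The fully taken part supplies 0.7·1625 = 1137.5 of 2500 enrollees, or 45.5%, against its 33.3% share of the list.

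**Illustrative bias (the contrast is an assumption).** Take prevalence 3.0% in the fully taken third and 1.65% elsewhere, so the true value is (3.0 + 2·1.65)/3 = 2.1%.
- Initial draw only: 0.5·3.0 + 0.5·1.65 = 2.33%.
- After top-ups: 0.455·3.0 + 0.545·1.65 = 2.26%.

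With a twofold contrast and the same true 2.1%, the value after top-ups is 0.455·3.15 + 0.545·1.575 = 2.29%. With the contrast reversed it is 0.455·1.26 + 0.545·2.52 = 1.95%. With no contrast the bias is zero.

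**Weights for a list already drawn.** In the first illustration, weights of 1 and 2 (that is, x and x+1) give the first part a share of 0.455/(0.455 + 2·0.545) = 0.294 and an estimate of 1.65 + 0.294·1.35 = 2.05%, an over-correction. Weights of 1 and 1.669 give a share of 0.333 and return 2.10%.

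**A single fractional interval.** With a random start and interval N/3250 at N = 4875, 4000 simulated draws gave inclusion rates of 0.661 to 0.671 against 0.667 expected.

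**The case against.** The strongest reply is that the text speaks of proportions of the list and does not say that they are consecutive blocks, which comes first, or that the split is fixed. If the two intervals were interleaved at random, or the split point chosen at random on a circular list, every resident would have the same marginal probability. The draw is called random in two places, and a journal article may leave list handling to the full protocol.

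Part of this stands. That one end of the register is favoured, or that whole consecutive households are taken, is something a reader might infer, but the article states no list order and no position for the parts. The absence of a stated random start is not counted as a fault either, and a random start within each part would not equalise the two rates. What does not stand is the rescue by interleaving: the article gives a specific rule, and nothing in it describes a randomised split.

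Four further replies have force. Actual list sizes are unknown and 2:1 is a ceiling. Top-ups at x = 1 reduce the imbalance. The illustrated bias is for one community, and the national estimate would take it over in full only if the contrast had the same sign across communities. Finally, the article never promises equal probabilities: a fixed 2500 per community already makes them unequal between communities. The primary objective is also aetiological, and no effect on hazard ratios is shown here.

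**Conclusion.** The point holds as a flaw in the stated selection rule. Within a community, residents have probability 1/x or 1/(x+1) according to the part of the register they fall in. The initial-draw ratio is 2 for lists between 3,250 and 6,500, 1.5 at x = 2 and 1.2 at x = 5, with no difference at exact multiples of 3250. For N = 4875 and 30% non-response it is about 1.67 after top-ups.

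A reader might infer that prevalence and incidence will be biased. The documents do not support that, because bias needs list order to be related to depression and the order is not given. The 2.26% against 2.1% is one illustration for one community, resting on an assumed contrast and an assumed list size.

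A reader might also infer that nothing in the analysis could correct the imbalance. That goes too far as well. The poststratification variables are not named, and weights on them would help where they coincide with list position, though not otherwise. An analysis plan that is not shown may add base weights.

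The rule should be changed because the inequality is avoidable, not because harm has been demonstrated.

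**What to change.** Replace the two-interval rule with either a computer-generated simple random sample of the register, or systematic sampling with a random start and the single fractional interval N/3250. Either gives each listed resident probability 3250/N in the initial draw and still yields 3250 people. Use the same method for top-up draws and for the annual replacement of people lost to follow-up.

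Record each person's selection probability in the data set. Where a list has already been drawn under the published rule, weight by the inverse of the overall selection probability with top-up draws included, not simply by x or x+1.

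The cost is a short script run on the list extracted from the community health service center. The Quality control section already provides for procedures to be revised after the local pilot studies, so a route for the change exists. For lists already drawn, the cost is reconstructing the selection probabilities from the draw records.

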#### Sample size

Based on a previous cross-sectional epidemiological study, the prevalence of major depressive disorder among adults in China was 2.1% [33]. Using version 15.0 of the Power Analysis & Sample Size (PASS) package, a sample size of 79,986 is required to identify a condition with a prevalence of 2.1% with a 95% confidence interval of 2.0% to 2.2%. We conservatively decided on a total target cohort of 85,000. This sample will be equally divided between the 34 sampled communities, that is, 2500 individuals in each community. Considering a potential non-response rate of 30% [34], the baseline recruitment will approach at least 3250 adults in each community. Individuals who are lost to follow-up after enrollment will be replaced annually by other individuals who live in the same community, maintaining the cohort size to a minimum of 2500 individuals at each primary sampling site throughout the 5 years of the project.

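### The 79,986 sample size assumes independent, fully diagnosed people, so 34 clusters of 2,500 with partial diagnostic interviewing do not support the stated 2.0% to 2.2% interval

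*Protocol article*

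**What the plan says.** The Sample size section of the protocol article starts from an earlier survey in which "the prevalence of major depressive disorder among adults in China was 2.1" per cent. From that prevalence it concludes that "a sample size of 79,986 is required to identify a condition with a prevalence of 2.1% with a 95% confidence interval of 2.0% to 2.2" per cent. It continues: "We conservatively decided on a total target cohort of 85,000", and "This sample will be equally divided between the 34 sampled communities, that is, 2500 individuals in each community". The only other allowance in that section is 30% for non-response, which concerns recruitment and not variance.

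Three features of the design appear elsewhere in the article:

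- Sampling method: "the third stage of sampling was to select a single community within each of the 34 DSP". These communities are the primary sampling units.
- Enrollment and baseline evaluation: the SCID interview is given to everyone classed as high-risk, and "in 40% participants classified as moderate-risk of depression and in 10% participants classified as low-risk of depression".
- Data analyses: "Poststratification weights will be used to estimate the national prevalence and incidence of depression".

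**The concern.** The sample-size statement ties a required number of people to a specific interval for national prevalence. That link holds only if the people are independent and each one's diagnosis is known. Neither holds here. People in one community share the environment and services that the study itself treats as possible causes of depression, and many moderate- and low-risk participants will have no baseline diagnosis.

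This is the article's only quantitative justification for the cohort size. If it stands, readers will expect a national prevalence good to ±0.1 points. Regional descriptions and time trends, which rest on fewer communities, may be read with the same confidence.

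**Working it through.** **Inputs from the article.** p = 0.021; 95% confidence; total width 0.002; N = 85,000; 34 communities of m = 2,500; interview fractions f = 1, 0.4 and 0.1 in the high-, moderate- and low-risk strata.

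**Assumed, because the article gives neither.** The ICC, and the share of true cases that do not screen high-risk.

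**1. Reproducing the stated figure.** For a single binomial sample at p = 0.021, the Clopper-Pearson 95% interval has width 0.0020000038 at n = 79,985 and 0.0019999912 at n = 79,986. So 79,986 is the first n that meets the target. The Wald formula gives 1.96² × 0.021 × 0.979 / 0.001² ≈ 78,977. The stated number is therefore correct for independent, fully diagnosed people, and no clustering or verification factor is contained in it.

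**2. The margin.** 85,000 / 79,986 = 1.063; on the Wald basis, 85,000 / 78,977 = 1.076. With DEFF = 1 + (2,500 − 1) × ICC, the largest ICC that keeps the stated width is 0.063 / 2,499 ≈ 0.000025, or 0.076 / 2,499 ≈ 0.00003. The implied between-community SD of prevalence, √(ICC × p(1 − p)), is about 0.07 to 0.08 percentage points.

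**3. Clustering alone at N = 85,000.** The half-width under independence is 1.96 × √(0.021 × 0.979 / 85,000) = 0.0964 points, which is multiplied by √DEFF.

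| Assumed ICC | Between-community SD (points) | DEFF | Half-width (points) | Interval |
|---|---|---|---|---|
| 0.0001 | 0.14 | 1.25 | 0.108 | 1.99–2.21% |
| 0.0005 | 0.32 | 2.25 | 0.145 | 1.96–2.24% |
| 0.001 | 0.45 | 3.50 | 0.180 | 1.92–2.28% |
| 0.005 | 1.01 | 13.5 | 0.354 | 1.75–2.45% |
| 0.01 | 1.43 | 26.0 | 0.491 | 1.61–2.59% |

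At ICC 0.01 the effective sample is 85,000 / 25.99 ≈ 3,270. Holding the stated interval with 2,500 per community would take 79,986 × 3.499 / 2,500 ≈ 112 communities at ICC 0.001.

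**4. Second-phase sampling alone.** The variance is [p(1 − p) + Σ W_h p_h(1 − p_h)(1/f_h − 1)] / N. Since 1/f − 1 is 0, 1.5 and 9 for the high, moderate and low strata, the variance factor is close to 1 + 1.5 × (share of cases in moderate) + 9 × (share of cases in low). Computed in full:

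| Cases not screening high-risk | Moderate / low | Factor |
|---|---|---|
| 0% | 0 / 0 | 1.00 |
| 5% | 3% / 2% | 1.23 |
| 10% | 6% / 4% | 1.46 |
| 20% | 12% / 8% | 1.91 |
| 30% | 15% / 15% | 2.60 |

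These factors barely move when the high/moderate/low split of participants is varied from 10/20/70 to 40/20/40; the case shares drive them. The 1.063 margin is used up by about 0.7% of cases in the low-risk stratum (9 × 0.007 = 0.063) or about 4% in the moderate-risk stratum (1.5 × 0.042 = 0.063).

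**5. Both together.** Total factor = 2,499 × ICC + second-phase factor; half-width = 0.0964 × √(total factor).

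| ICC | Factor 1.00 | Factor 1.23 | Factor 2.60 |
|---|---|---|---|
| 0.0001 | ±0.108 | ±0.117 | ±0.163 |
| 0.001 | ±0.180 | ±0.186 | ±0.218 |
| 0.01 | ±0.491 | ±0.494 | ±0.506 |

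At ICC 0.001 or more, clustering dominates. The effect of the poststratification weights is not included, because the article gives nothing from which to compute it.

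**The case against.** **Stronger readings that the article does not support.**

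- A reader might infer that the arithmetic is wrong. It is not; 79,986 reproduces exactly. The fault is in its assumptions.
- A reader might infer that prevalence intervals will be two to five times as wide as stated. That presumes an ICC of roughly 0.001 to 0.01. At 0.0001 to 0.0005 the half-width from clustering is ±0.11 to ±0.145, which misses the target but is well under double it.
- A reader might infer a fixed second-phase penalty. There is none if every case screens high-risk. The high-risk definition is broad (GHQ-12 of at least 5, or any one of 12 further items), which favours a small loss.
- A reader might infer that the published intervals will be falsely narrow. The Sample size section plans no interval calculation, and the variance method may be set out in an analysis plan that is not shown.

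**What else can be said for the plan.** Stratifying by region and by urban/rural status could remove some between-community variance, and DEFF = 1 + (m − 1) × ICC gives no credit for that. The Aims section concerns aetiology, subtypes and mechanisms; prevalence belongs to the descriptive set of analyses. Both points stand, and they limit the consequences.

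**Why this does not rescue the claim.** The article itself asserts an interval and the number required for it. A later choice of variance estimator cannot restore precision that 34 clusters do not supply. The sample-size section also takes no credit for stratification.

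**Conclusion.** The sample-size statement is wrong as written. The stated 2.0% to 2.2% interval fails at any ICC above about 0.000025 to 0.00003, a between-community SD of about 0.07 to 0.08 points. Such near-uniformity across urban and rural sites in 17 provinces would sit badly with a study that collects community climate, pollution and socio-economic measures (Table 2) because they may influence depression.

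That threshold follows from the article's own figures and the usual equal-cluster design effect. How far the interval widens does not: ±0.1 to ±0.5 points is a scenario range for ICC 0.0001 to 0.01, with assumed case shares outside the high-risk stratum of 0% to 30%. The finding does not show that 85,000 is too few for the study's aims.

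**What to change.** Keep 85,000. In the Sample size section:

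- Remove the 2.0% to 2.2% claim and the description of the target as conservative.
- Restate the expected precision from DEFF = 1 + (2,500 − 1) × ICC combined with the 1/0.4/0.1 second-phase variance. Show it over a stated ICC range (for example 0.0001 to 0.01, about ±0.1 to ±0.5 points) and for stated shares of cases outside the high-risk stratum.

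For the analysis, compute prevalence intervals with community as the sampling unit and with the second-phase weights. Each province-by-urban/rural cell holds one community, so cells must be collapsed to estimate variance. Note also that sites were not chosen purely at random, as the limitations in the Discussion acknowledge, so a design-based interval carries that caveat.

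Cost: a rewritten paragraph, a less favourable stated precision and slightly more analysis work. No extra participants are needed.

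### The allowance for 30% non-response multiplies by 1.3 instead of dividing by 0.7, so the draw of 3,250, the top-up factor and the community minimum are all too small

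*Protocol article*

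**What the plan says.** All references are to the protocol article.

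- **Target.** Sample size: "This sample will be equally divided between the 34 sampled communities, that is, 2500 individuals in each community".
- **Number approached.** Sample size: "Considering a potential non-response rate of 30% [34], the baseline recruitment will approach at least 3250 adults in each community". Sampling method repeats it: "Initially 3250 eligible individuals will be randomly selected from the lists of residents". Step B under Enrollment and baseline evaluation gives the same 3,250.
- **Community minimum.** One selection criterion under Sampling method is "having a population of at least 3250 adults who are permanent residents (the minimum estimated sample required to enrolled 2500 adults".
- **Top-up.** If the first draw falls short, Sampling method again cites 30% non-response and says "the additional number will be defined as 1.3 times of the differences between 2500 and actual number". It adds that "this process will be repeated as needed until 2500 individuals have been enrolled". Top-ups come from listed residents who have not yet been selected.
- **Replacement.** Under Sample size, people lost to follow-up are replaced each year from the same community, so that each site keeps at least 2,500 over the 5 years.

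**The concern.** Three planning figures rest on one inflation step, and that step is wrong for the stated rate. If 30% of those invited do not respond, the number to invite is the target divided by the response proportion. Multiplying the target by one plus the non-response rate always gives too few.

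The slip matters most in the community minimum. An initial draw that is too small can be topped up, but a community that is too small cannot. The limitations in the Discussion say that communities unable to recruit 2,500 were left out, and the threshold given for that screen is 3,250. A community could therefore have been accepted although, on the plan's own response assumption, it is not expected to supply 2,500 people or any replacements.

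**Working it through.** **Inputs (all from Sample size and Sampling method).** Target 2,500 per community; 34 communities; non-response 30%, so response 70%; number approached 3,250; community minimum 3,250; top-up factor 1.3; stated requirement 79,986; total target 85,000.

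**1. Reproduce the plan's figure.** 2,500 × (1 + 0.30) = 3,250. This matches exactly, so the step used was multiplication by 1.3.

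**2. Correct inflation.** 2,500 / (1 − 0.30) = 3,571.4, so 3,572.

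**3. Expected yield of the stated draw.** 3,250 × 0.70 = 2,275, which is 225 (9%) below 2,500.

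**4. Rate at which 3,250 would be right.** 1 − 2,500/3,250 = 23.1%. The article states no such rate and does not define non-response in another way.

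**5. Top-up rule at 70% response.** Each round is expected to close 1.3 × 0.7 = 0.91 of the gap and to leave 9% open.

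| Round | Invited | Total invited | Expected enrolled |
|---|---|---|---|
| First draw | 3,250 | 3,250 | 2,275 |
| Top-up 1 | 292.5 | 3,542.5 | 2,479.8 |
| Top-up 2 | 26.3 | 3,568.8 | 2,498.2 |
| Top-up 3 | 2.4 | 3,571.2 | 2,499.8 |

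A single correct top-up would be 225/0.7 = 321.4 invitations. Both routes end at about 3,571 invitations.

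**6. Community at the minimum.** With 3,250 eligible adults the first draw invites everyone. Expected enrolment is 2,275, and no uninvited resident remains. At 3,571 eligible adults the expectation is 3,571 × 0.7 = 2,499.7. The vulnerable band is therefore about 3,250 to 3,571 eligible adults. The minimum counts adult permanent residents, while the draw is from eligible residents, and Sample criteria also excludes people in institutions. The number who can be invited may thus be somewhat below the count used for selection.

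**7. Worst-case total.** 34 × 2,275 = 77,350. Under the simple binomial calculation at 2.1% prevalence, the half-width at 77,350 is 0.101 percentage points (Wald) or 0.102 (exact), against the planned 0.10. The plan's 79,986 reproduces with the exact (Clopper-Pearson) interval.

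**8. Replacement (illustration only).** The article gives no attrition rate. If 5% to 10% were lost each year for 5 years, a site would need 2,500 × 0.05 × 5 = 625 to 2,500 × 0.10 × 5 = 1,250 replacements. At 70% response that means 3,125/0.7 ≈ 4,460 to 3,750/0.7 ≈ 5,360 eligible adults in all.

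**The case against.** The strongest reply is that 3,250 is only a first draw. The text says at least 3,250 will be approached, and the top-up repeats until 2,500 are enrolled. Step 5 shows that this ends at practically the same number of invitations as a correct single draw. This stands: wherever the register is long enough, final enrolment is unaffected and the cost is a few small extra rounds.

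It is also fair that no community is shown to lie in the vulnerable band. The surveillance points average roughly 500,000 people (over 300 million across 605 points). Each point contains a variable number of communities, however, so this does not settle the size of those chosen. The risk is neither demonstrated nor excluded.

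A reader might infer that the cohort will end at 77,350, below both 85,000 and the stated requirement of 79,986. The documents do not support that. It would need every community to sit at the minimum, or the repeat rule to be ignored, and even then the loss of precision is negligible.

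A reader might also take the replacement illustration as a shortfall caused by the factor of 1.3. It is not: the attrition rate there is assumed, and a minimum of 3,572 would leave no reserve either.

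The reply does not rescue the stated figures. A 30% non-response rate, 3,250 approached and 2,500 enrolled from that draw cannot all hold, and the repeat rule cannot help a community whose register is exhausted.

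**Conclusion.** The inflation is wrong as written, and the error runs through the initial draw, the top-up factor and the community minimum. At the plan's own 30%, the draw of 3,250 is expected to fall 225 (9%) short per site, each top-up closes 91% of the remaining gap, and 3,250 adults is not the smallest community expected to yield 2,500.

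In communities with enough residents, the consequence is misplanned workload. In any community with about 3,250 to 3,571 eligible adults, 2,500 is not expected to be reached and nobody is left for top-up or annual replacement. How many of the 34 are affected cannot be told from the article. These figures are expected values that take the 30% at face value in every community and in every round. The point should be fixed, but it does not threaten the study's precision.

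**What to change.** Either correct the numbers or change the assumption.

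1. Change the initial draw to 3,572 in Sampling method, in Sample size and in step B of Enrollment and baseline evaluation.
2. Replace 1.3 times the shortfall with shortfall/0.7 (a factor of 1.43).
3. Correct the stated community minimum to at least 3,572 eligible adults, and note that annual replacement needs a further reserve, sized from a stated attrition assumption.
4. Alternatively, keep 3,250 and 1.3, and state and justify non-response of about 23%.

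Under either option, check the register counts of the 34 chosen communities. Report any that is expected to fall short of 2,500, and restate the per-site figure for it. Site substitution need not be required: local pilots at all 34 sites have begun, and replacing a piloted community would not be cheap.

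The cost is 3,572 − 3,250 = 322 more first-round invitations per site, or 34 × 322 = 10,948 in total (121,448 against 110,500). At 30% non-response the top-up rounds would issue nearly all of these anyway. Target enrolment does not change. The article says procedures will be revised after the pilots, which is a natural point to make the correction.
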